#### Secondary Analyses

Secondary analyses focus on the analysis of intervention components on participants’ step counts and on the effects of incentives on app engagement, nonusage attrition, and motivation. Steps per day are analyzed using the same modeling approach as described above. Again, if missing data can be assumed to be missing at random, we plan to impute missing step counts using multiple imputations. As evidence suggests that participant days with less than 1000 steps are unlikely to represent accurate activity data [63,64], those days will be set to missing before imputation.

Generalized linear models will be used to analyze the effect of incentives on engagement and nonusage attrition. One-way analysis of variance (ANOVA) is performed for each subscale of the BREQ-2 to analyze the effect of incentives on the different forms of intrinsic and extrinsic motivation. *P* values will be adjusted according to the Holm-Bonferroni method [65]. If the omnibus test of the ANOVA is significant, we will investigate contrasts between the 3 incentive groups. Again, the main comparison of interest is between the intervention groups and the control group. An overview of all planned statistical analysis is available in Multimedia Appendix 2.

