### Study Design

From October to December 2017, insurees of a large Swiss health insurance used the Ally app over a 12-day baseline and a 6-week intervention period. During the baseline period, participants only had access to the dashboard of the app, and no interventions were administered. Over the course of the 6-week intervention period, we randomized participants to different versions of 3 intervention components: daily self-monitoring prompts (2 levels; within-subjects), a weekly planning intervention (3 levels; within-subjects), and daily incentives (3 levels; between-subjects). The rationale for these intervention components is described below. To meet study objective three, we aimed to explore if and how participants’ reaction to intervention components were dependent on their context. To do so, we ideally need to observe reactions to intervention notifications in a wide variety of contexts. We, therefore, sent out intervention and step goal–related notifications at random points in time but within prespecified time windows that guaranteed delivery at appropriate times. For example, daily step goal notifications were delivered at a random point in time between 8 am and 10 am as users likely expect to be notified about their goal early in the day. Participants completed a Web-based questionnaire at baseline and at postintervention follow-up and received CHF 10 (US $10 as of 2017) for the successful completion of both questionnaires. If participants provided consent, they were invited to participate in exit interviews after the end of the study that investigate perceptions of participants and mechanisms of behavior change.

The following subsections first describe details and rationale for each intervention component as well as for potential moderators. Subsequently, we outline how each component was randomized during the intervention period and how we define the proximal outcome to evaluate each component.

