### Randomization, Allocation Concealment, and Blinding

The MobileCoach version used in this study requires the time point of dissemination for all dialogues to be known a priori. Therefore, randomization had to be performed upon enrollment of participants for all intervention components. Each participant was randomized to 1 out of 3 incentive conditions using simple randomization and an allocation ratio of 1:1:1. In addition, participants were randomized to 1 out of 9 planning intervention sequences (S_1_-S_9_) that determine the order in which the participant received the AP intervention, the CP intervention, or CC intervention throughout the intervention period. We used blocked randomization with a block size of 9 to achieve balance between the sequences. The resulting intervention schedule (Table 1) is uniform and strongly balanced, which controls for time and carry-over effects [45]. To avoid interference of self-monitoring prompts and planning, self-monitoring prompts were not delivered on Sundays. Thus, subtracting 6 from 42 left 36 available days for delivering self-monitoring prompts. To prevent repetition of content, we created 18 different versions of self-monitoring prompts that we randomly allocated to the 36 days for each participant. Consequently, at each of the 36 days, half of participants received a self-monitoring prompt (on average), whereas the other half received no prompt. All randomizations were performed using random number sequences generated with the shuffle-array package in JavaScript.

The fully automated randomization process guarantees allocation concealment for everyone involved in the study. Variables in the dataset indicating intervention allocation are encrypted to blind members of the research team involved in data analysis. A researcher at the Swiss Federal Institute of Technology in Zurich who is not involved in data analyses holds the decryption key and is instructed to safely store the key until the analysis script has been finalized. Due to the setting of the study, it is not possible to blind participants to intervention assignments. To reduce the impact of performance and attrition bias, participants were not informed about the details of the intervention components before the study.

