For financial and charity incentives, postintervention differences in intrinsic and extrinsic motivation, and differences in app engagement and nonusage attrition during the intervention period are evaluated as additional secondary outcomes. Dimensions of intrinsic and extrinsic motivation are measured using the Behavioral Regulation for Exercise Questionnaire-2 (BREQ-2) [46]. As the external regulation subscale in the BREQ-2 exclusively relates to external regulation by other people, it is substituted by the more generally worded external regulation subscale of the Situational Motivation Scale (SIMS) [47]. Subscales of both instruments have shown good reliability (Cronbach alpha=.73-.86, BREQ-2 [46] and Cronbach alpha=.86, SIMS external regulation subscale [47]). Validity has been confirmed by factor analysis (BREQ-2) [46] and correlational analysis (SIMS) [47]. We measure engagement with the Ally app using the number and length of app launch sessions per day. An app launch session is defined as any interaction of the participant with the Ally app, separated by 5 min between events. If a participant left the app open and did not take action for 5 min or more, then the next interaction with the app counts as a new session. We coded a participant as “non-usage attrition observed” when she/he stopped using the Ally app at least 7 days before the end of the study.

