#### Primary Analyses

To evaluate main effects and interactions of intervention components, we will use the centered and weighted GEE approach described in the study by Boruvka et al [62]. This approach guarantees unbiased effect estimates when treatment and moderator variables are time-varying. Statistical models will evaluate each main effect and interaction of intervention components of interest on the components appropriate proximal outcome. For all main effects and interactions that include comparisons of multiple conditions, the main comparisons of interest are between the respective intervention and control conditions.

Missing data on covariates and on the dependent variable will be imputed using multiple imputation, provided the missing at random assumption is justified. We will perform sensitivity analyses to assess the robustness of the results of the primary analyses. These analyses include a per-protocol analysis and an adjusted analysis in which effect estimates are adjusted for a linear trend of time, baseline step count, and covariates of physical activity. For all tests, we use 2-sided *P* values with alpha<.05 level of significance.

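### The engagement model as described names no pre-intervention app-use covariate, although the app was in use for 12 intervention-free days; adding one would be a cheap gain in precision for a secondary outcome

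*Protocol article*

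**What the plan says.** The Primary and Secondary Outcomes section under Measurements makes engagement a secondary outcome for the incentive arms: "differences in app engagement and nonusage attrition during the intervention period are evaluated as additional secondary outcomes". The measure is defined there: "We measure engagement with the Ally app using the number and length of app launch sessions per day".

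Secondary Analyses gives the method in one sentence: "Generalized linear models will be used to analyze the effect of incentives on engagement and nonusage attrition". It states no distribution, link or covariates. The same section ends by pointing elsewhere: "An overview of all planned statistical analysis is available in Multimedia Appendix 2". That appendix is not shown.

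Study Design describes a period of app use before the intervention: "insurees of a large Swiss health insurance used the Ally app over a 12-day baseline and a 6-week intervention period". On what was active then, it says: "During the baseline period, participants only had access to the dashboard of the app, and no interventions were administered".

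The one baseline adjustment in the article is under Primary Analyses, among the sensitivity analyses: "an adjusted analysis in which effect estimates are adjusted for a linear trend of time, baseline step count, and covariates of physical activity".

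On allocation, the Randomization section says: "Each participant was randomized to 1 out of 3 incentive conditions using simple randomization and an allocation ratio of 1:1:1". Blocking is described only for the planning sequences.

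**The concern.** The incentive comparison is between participants, so its standard error carries the full person-to-person variation in app use. The prompt and planning comparisons are partly protected because each participant serves as their own control; this one is not. How often someone opens an app is likely to vary a good deal between people and to persist to some degree within a person. A 12-day record taken before any intervention is therefore a natural covariate, and the engagement analysis as described does not mention it. Where the article does describe baseline adjustment, it is for steps and for the primary analyses only.

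What is at stake is efficiency. The sample size was set for the incentive-by-planning interaction on step-goal achievement, so no stated calculation assures power for engagement. If the contrast is run without the covariate, a real effect of incentives on engagement is easier to miss than it needs to be.

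**Working it through.** The article gives no power or precision figure for engagement, so there is none to reproduce. Its sample size of roughly 220 concerns a different effect and is not disputed here.

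**Inputs from the article**
- Enrolled: 274. Stopped using the app before the intervention period: 32 (Results, Recruitment). Remaining: 274 − 32 = 242.
- Three incentive arms at 1:1:1, so about 242/3 = 80.7 per arm, or 274/3 = 91.3 if all enrolled participants are analysed.
- Two-sided test at 0.05.

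**Inputs assumed**
- ρ, the correlation between a participant's mean engagement at baseline and during the intervention: 0.3, 0.5 and 0.7. The article gives none.
- d, the standardized difference between an incentive arm and control: 0.3 and 0.4, for illustration.

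**Step 1: variance.** For a per-participant mean in a linear model, adjusted variance / unadjusted variance = 1 − ρ².
- ρ = 0.3: 1 − 0.09 = 0.91, a 9% reduction.
- ρ = 0.5: 1 − 0.25 = 0.75, a 25% reduction.
- ρ = 0.7: 1 − 0.49 = 0.51, a 49% reduction.

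**Step 2: smallest difference detectable with 80% power.** MDE = (1.96 + 0.84) × √(2/m) × √(1 − ρ²), in SD units, with m per arm. For m = 80.7, √(2/m) = 0.157.

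| Analysed | Unadjusted | ρ = 0.3 | ρ = 0.5 | ρ = 0.7 |
|---|---|---|---|---|
| 242 | 0.441 | 0.421 | 0.382 | 0.315 |
| 274 | 0.415 | 0.395 | 0.359 | 0.296 |

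**Step 3: power with 242 analysed.** Power = Φ( d / [√(2/m) √(1 − ρ²)] − 1.96 ). For d = 0.4 unadjusted: 0.4/0.157 − 1.96 = 0.58, and Φ(0.58) = 0.72.

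| d | Unadjusted | ρ = 0.3 | ρ = 0.5 | ρ = 0.7 |
|---|---|---|---|---|
| 0.4 | 72% | 76% | 84% | 95% |
| 0.3 | 48% | 52% | 60% | 76% |

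At ρ = 0.3 the gain is about 4 points; at ρ = 0.5 it is about 12.

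**Step 4: limits of the approximation.** The factor 1 − ρ² belongs to linear adjustment of a continuous mean. It is only a guide for session counts under a log link. It does not carry over to a binary attrition outcome in a logistic model, where adjustment also changes the odds ratio being estimated.

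**The case against.** The strongest reply is that the article does not say the model is unadjusted. A generalized linear model admits covariates, the sentence excludes none, and the covariates of a secondary model are the kind of detail a condensed article leaves to an appendix. This stands. A reader might infer that the authors decided against baseline adjustment; the text supports only that no such term is named.

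A reader might also infer that simple randomization leaves the unadjusted contrast biased by chance differences in prior app use. It does not. The contrast is unbiased in expectation, and its standard error already allows for chance imbalance.

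Three further points stand in part:
- Baseline use was dashboard only, whereas later sessions can be triggered by goal messages, evening feedback, prompts and planning dialogues. The Strengths and Limitations section also reports a larger fall in use early in the study. Either could make ρ modest.
- The article does not say that session number and length were logged at baseline. It knows that 32 people stopped using the app before the intervention, so some use was observed, but that does not establish daily session records.
- Randomization took place at enrollment, so baseline app use comes after allocation. Table 2 gives dashboard and chat as the mode of delivery for incentives, and the dashboard was open during baseline. The statement that no interventions were administered then, together with the nondisclosure described under Randomization and under Recruitment and Eligibility, makes early disclosure of the arm unlikely but does not expressly exclude it.

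These points limit the size of the gain and set conditions on the change. They do not remove the case for making it.

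**Conclusion.** The point holds as an efficiency improvement for a secondary outcome and is not a validity error. The article names no pre-intervention app-use term for engagement, and the design offers a natural one. If the contrast is run without it, the variance forgone is about 9%, 25% or 49% at an assumed ρ of 0.3, 0.5 or 0.7, with the low end quite possible. These figures rest on an assumed correlation, a linear approximation and arms of equal size; the power figures also rest on an assumed effect size. No comparable gain can be claimed for nonusage attrition.

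**What to change.** Before the allocation key is released, state in the analysis script whether the engagement models include baseline app use. If they do not, add it:
- In the model for session number, use each participant's mean daily number of app launch sessions over the 12-day baseline; in the model for session length, use the corresponding baseline length. Participants with no baseline sessions take the value zero.
- Make this the stated analysis and keep the unadjusted contrast as a sensitivity analysis.
- First confirm that sessions were logged at baseline and that the incentive arm was not disclosed before the intervention period. If either fails, keep the unadjusted contrast.
- If the covariate is also put in the attrition model, report the odds ratio as conditional on prior use and claim no comparable gain in precision.

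The cost is one covariate in the script and a check of the baseline app logs, with no new participants or data collection if the logs exist. The timing allows it: the article says that analysis starts only after its publication and that the decryption key is held until the script is final, so the choice can be made blind to allocation.

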#### Other Outcomes

As a preliminary pre-post evaluation of the Ally app, self-reported health outcomes and targeted mediators of behavior change were assessed at baseline and at postintervention follow-up. In addition, we assessed participant’s perceptions of the Ally app, of intervention components, and of the chatbot in addition to predictors of technology acceptance at postintervention follow-up. An overview of all measured variables is available in Multimedia Appendix 1 ([49-57]).

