## Results

### Recruitment

Of all 30,000 invited insurees, 749 (2.50%) clicked the link in the invitation mail and were subsequently screened for eligibility. Of those, 694 (92.7%) were eligible and 382 (51.0%) provided informed consent to participate. Of all insurees who provided informed consent, 274 (71.7%) successfully completed the baseline survey and installed the Ally app on their smartphone (Figure 3). Invited insurees were given the opportunity to select reasons why they declined participation from a list of predefined answer options using a separate survey (n=191). A link to this survey was included in the invitation mail and placed on the informed consent screen. Possession of an incompatible smartphone (37/191, 19.4%) and unwillingness to share smartphone sensor data (35/191, 18.3%) were the most frequently stated reasons to decline participation.

Of 274 participants, 32 (11.7%) did not receive any interventions because they stopped using the app before the start of the intervention period. Due to technical errors, 6 participants did not receive the interventions they were randomized to (eg, a self-monitoring prompt was sent out on a day where the participant was randomized to not receiving a prompt). For the 6 participants, these errors affected between 1 and 25 out of 42 participant days. Steps per day measured with the smartphone are available for 227 (82.8%, 227/274) participants, and smartphone sensor data are available for 247 (90.1%, 247/274) participants. After completing the 6-week intervention period, 181 (66.1%, 181/274) participants filled out the Web-based follow-up survey. Data collection finished in January 2018.

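### Motivation is tested by an unadjusted post-only ANOVA; adding a baseline covariate would make a valid test more precise at almost no cost

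*Protocol article*

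**What the plan says.** The Protocol article, under Primary and Secondary Outcomes, lists "postintervention differences in intrinsic and extrinsic motivation" among the secondary outcomes for the incentive arms. Motivation is measured with the BREQ-2, whose external regulation subscale is replaced by the one from the SIMS. Secondary Analyses fixes the test: "One-way analysis of variance (ANOVA) is performed for each subscale of the BREQ-2 to analyze the effect of incentives". For multiplicity, the P "values will be adjusted according to the Holm-Bonferroni method", and contrasts between arms follow only when the omnibus test is significant. No covariate is named. Baseline adjustment appears only under Primary Analyses, as a sensitivity analysis of the step-goal models.

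On baseline data, Study Design says: "Participants completed a Web-based questionnaire at baseline and at postintervention follow-up". Other Outcomes adds that "self-reported health outcomes and targeted mediators of behavior change were assessed at baseline and at postintervention follow-up". Neither section names the BREQ-2 or the SIMS in connection with baseline, and Table 4 shows no baseline motivation score. The appendices that list the variables and analyses are not shown.

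On allocation: "Each participant was randomized to 1 out of 3 incentive conditions using simple randomization and an allocation ratio of 1:1:1". On follow-up, Recruitment reports that "181 (66.1%, 181/274) participants filled out the Web-based follow-up survey".

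**The concern.** A one-way ANOVA on follow-up scores leaves all stable between-person variation in motivation in the error term. A score on the same scale before the intervention usually explains part of that variation. Where such a score exists, leaving it out gives up precision that costs nothing to recover.

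The comparison matters to the trial's argument. The Incentives section proposes charity donations because cash may weaken intrinsic motivation, and this is the analysis that examines that idea. It rests on 181 completers in three arms, and it must pass both an omnibus test and a Holm adjustment.

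**Working it through.** The article states no power, SD or effect size for motivation, so there is no planned figure to reproduce. The targets of 220 and 300 in Sample Size concern the incentive-by-planning interaction on step goals.

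**Inputs from the article**
- Completers: 181 of 274 = 66.1%, as stated; 274 − 181 = 93 have no follow-up score.
- Three arms at 1:1:1 by simple randomisation.
- Two-sided alpha of .05.

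**Assumptions**
- Completers are spread evenly: 181/3 = 60.3 per arm.
- Follow-up SD = 1, so effects are in SD units.
- Both incentive arms differ from control by 0.4 SD.
- The baseline/follow-up correlation r is .3, .5 or .7.

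**Formulas**
- ANCOVA residual variance relative to ANOVA: 1 − r².
- Equivalent number of completers in a post-only analysis: 181/(1 − r²).
- Pairwise difference detectable with 80% power at .05: (1.96 + 0.84) × √(2/60.3) × √(1 − r²). Post-only, this is 2.80 × 0.182 = 0.51 SD.
- Omnibus power: noncentral F on 2 and 178 df (177 with the covariate), with noncentrality 60.3 × (2/3) × 0.4²/(1 − r²). Post-only, the noncentrality is 6.4.

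| Analysis | Residual variance | Equivalent completers | Detectable difference (SD) | Omnibus power |
|---|---|---|---|---|
| Post-only ANOVA | 1.00 | 181 | 0.51 | 0.61 |
| ANCOVA, r = .3 | 0.91 | 199 | 0.49 | 0.65 |
| ANCOVA, r = .5 | 0.75 | 241 | 0.44 | 0.74 |
| ANCOVA, r = .7 | 0.51 | 355 | 0.36 | 0.89 |

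A simulation with 181 participants, simple 1:1:1 allocation and 4,000 runs per scenario agrees. Power at 0.4 SD was about 0.60 for ANOVA, against 0.64, 0.72 and 0.89 for ANCOVA at r = .3, .5 and .7.

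**Validity.** In the same simulations, the type I error of the post-only ANOVA was 0.044 to 0.050.

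**Chance imbalance.** The standard error of a baseline difference between two arms is √(2/60.3) = 0.18 SD. A difference above 0.2 SD has probability 0.27 for one comparison, and 0.44 for at least one of the two comparisons with control.

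**Holm.** These figures are before the Holm adjustment, because the article does not give the number of tests. Absolute power under Holm is lower. The proportional fall in the detectable difference, √(1 − r²), is the same at any significance level.

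**The case against.** The strongest objection is that the enabling fact is missing: nothing in the article says that the motivation subscales were asked at baseline. A reader might infer it from the baseline questionnaire and from the statement about targeted mediators. That makes it likely, since the Incentives section expects incentives to raise motivation, but the article never names these scales as measured twice. It therefore does not show that the plan throws away data it holds. This stands, and the recommendation is conditional for that reason.

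A reader might also infer that chance baseline differences bias the comparison. They do not: under randomisation they are already reflected in the ANOVA standard error, as the simulated type I error shows. Nor is the post-only ANOVA the least precise option. A change score has variance 2(1 − r), which is 1.4 at r = .3 and so worse than post-only whenever r is below .5.

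The size of the gain also depends on an assumed correlation and a hypothetical effect; at r = .3 it is modest. The fallback covariates have no documented link to motivation, and Table 4 shows missing values for sex (5) and IPAQ (6).

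Finally, selective dropout among the 93 without a follow-up score could matter more than precision. The article does not show whether dropout is selective. A baseline covariate would help only with the part that it explains.

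**Conclusion.** The plan fixes an unadjusted post-only comparison for motivation where a baseline-adjusted one would be more precise. The planned test is valid; the loss is in efficiency.

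If the subscales exist at baseline and r lies between .3 and .7, residual variance falls by 9% to 49%. Omnibus power then rises from about 0.61 to 0.65–0.89, given even arms of about 60, a 0.4 SD difference of both incentive arms from control, and no Holm adjustment. If the subscales do not exist at baseline, these figures do not apply and the gain from other covariates is unknown. The point is a low-priority, free improvement on a secondary outcome.

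**What to change.** State whether the BREQ-2 subscales and the SIMS external regulation subscale were in the baseline questionnaire.

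- **If they were:** replace each one-way ANOVA by ANCOVA of the follow-up subscale on incentive arm plus the baseline score of the same subscale. Keep the omnibus test, the contrasts and the Holm adjustment. The cost is one model term per analysis and no new data.
- **If they were not:** say so, and adjust for a prespecified set of baseline variables that Table 4 shows were collected: age, sex, IPAQ and SF-12 mental score. Specify a simple rule for the few missing covariate values. The cost is several terms and that rule.

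The choice can still be fixed blind. Under Expected Results and Dissemination, analysis begins only once the article is published, and under Randomization, Allocation Concealment, and Blinding, the allocation key is withheld until the script is final.

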**Conclusions:**

This study describes the evidence-based development of a JITAI for increasing physical activity. If components prove to be efficacious, they will be included in a revised version of the app that offers scalable promotion of physical activity at low cost.

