#### Incentives

Meta-analyses [35,36] and recent randomized trials [37-39] have demonstrated the ability of financial incentives to increase physical activity. However, financial incentives may reduce intrinsic motivation [40,41]; thus, charity incentives have been proposed as an alternative incentive strategy. Charity incentives, that is, donations to a charity organization, could foster experiences of autonomy and relatedness, which are known to facilitate rather than impede the buildup of intrinsic motivation [42]. Moreover, 2 recent studies have so far compared financial and charity incentives with mixed results [37,43].

In this study, participants were randomly allocated to either a financial incentive, a charity incentive, or a control condition using an allocation ratio of 1:1:1. In the financial incentive condition, participants received CHF 1 (US $1 as of 2017) for each day they met their personalized step goal. In the charity incentive condition, instead of keeping the reward to themselves, participants made a donation of CHF 1 to a charity of their choice. Participants allocated to the control condition received no incentives. Earned rewards (maximum of CHF 42) were paid to participants or donated to charity after completion of the study.

We hypothesize that the presence of incentives moderates the effect of the other intervention components. Both planning and self-monitoring prompts target the participants’ self-regulatory processes and thus require the participant to be motivated to reach the provided step goals to produce an effect [44]. As we expect the incentives to increase the motivation of participants, we hypothesize that effects of self-monitoring prompts and planning are more pronounced for participants receiving financial or charity incentives.

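### The cash-versus-control difference in intrinsic motivation is examined only after a significant three-group omnibus test, so the concern the protocol itself raises may go unestimated

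*Protocol article*

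**What the plan says.** The Incentives section gives the reason for the charity arm: "financial incentives may reduce intrinsic motivation [40,41]; thus, charity incentives have been proposed as an alternative incentive strategy". The concern is attached to cash. Charity is expected, if anything, to support intrinsic motivation.

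The Primary and Secondary Outcomes section lists among the additional secondary outcomes: "For financial and charity incentives, postintervention differences in intrinsic and extrinsic motivation".

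The Secondary Analyses section says a one-way ANOVA "is performed for each subscale of the BREQ-2 to analyze the effect of incentives on the different forms of intrinsic and extrinsic motivation". It then says that P values are Holm-Bonferroni adjusted, without saying whether the family is the omnibus tests across subscales, the contrasts, or both. Next comes the condition: "If the omnibus test of the ANOVA is significant, we will investigate contrasts between the 3 incentive groups". The sentence after that names each incentive group against control as the comparison that matters most.

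The Recruitment results report follow-up questionnaires from 181 of 274 participants (66.1%).

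**The concern.** The comparison the section calls most important is reached only through a different and less focused test. The omnibus F spreads its sensitivity over all differences among three arms, whereas the question raised in the Incentives section is one difference, cash minus control, on one construct.

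If the omnibus test is not significant, nothing in the stated plan calls for that difference or its interval. A reader would then have a non-significant P value and no means of telling a difference near zero from one of moderate size measured imprecisely. With a third of participants missing from the follow-up questionnaire, imprecision is likely. The trial could end without a usable statement on the very effect that motivated its third arm.

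**Working it through.** **The plan's own figure.** There is none for motivation. The stated sample size of roughly 220 concerns the incentive-by-planning interaction on step goals and has no bearing here.

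**Inputs from the article.** Allocation 1:1:1; 181 responders, so 181/3 ≈ 60 per arm; two-sided alpha .05; three-group ANOVA; contrasts only if the omnibus test is significant.

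**Assumptions not in the article.** Responders evenly spread over arms; normal outcome with common SD; a loss under cash of 0.3 to 0.6 SD; four or five subscales in the Holm family, giving a first step of .05/4 = .0125 or .05/5 = .01.

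**Step 1, precision.** Half-width of the 95% interval for cash minus control, in SD units, with 3 × 59 = 177 degrees of freedom:

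t(.975, 177) × √(2/60) = 1.973 × 0.1826 = 0.36.

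Even an observed difference of exactly zero leaves losses up to 0.36 SD inside the interval.

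**Step 2, what a closed gate can hide.** The critical F(2, 177) at .05 is about 3.05.

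- Observed charity mean equal to control: F = 60d²/3, so the gate stays shut up to d = √(3 × 3.05/60) = 0.39 SD.
- Observed charity mean midway between cash and control: F = 60d²/4, so it stays shut up to d = √(4 × 3.05/60) = 0.45 SD.

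Both exceed the 0.36 SD at which the direct contrast would reach .05.

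**Step 3, how often the gate is shut.** For a true 0.4 SD loss with charity equal to control, the noncentrality is 60 × 0.4² × 2/3 = 6.4. The omnibus power at .05 is then about 0.61, so in about 39% of such trials the contrast would not be examined.

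**Step 4, power to show the loss.** Simulation with 60 per arm and charity equal to control. The gated columns require a significant omnibus test and then a contrast significant at .05 in the harmful direction.

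| True loss (SD) | Direct, .05 | Gate at .05 | Gate at .0125 | Gate at .01 |
|---|---|---|---|---|
| 0.3 | 0.37 | 0.29 | 0.16 | 0.15 |
| 0.4 | 0.59 | 0.51 | 0.35 | 0.33 |
| 0.5 | 0.78 | 0.73 | 0.59 | 0.57 |
| 0.6 | 0.91 | 0.89 | 0.80 | 0.78 |

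**Step 5, separating the gate from the adjustment.** At 0.4 SD, a direct contrast with no gate but tested at .01 has power 0.34, essentially the 0.33 found with the .01 gate. A direct contrast with Dunnett adjustment for two comparisons with control has 0.48, close to the 0.51 of the .05 gate. The large drop therefore comes from the stricter significance level. The gate itself costs about 0.59 − 0.51 = 0.08.

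**Step 6, sensitivity to the charity arm.** At 0.4 SD with a gate at .0125, power is 0.27 if charity falls halfway between cash and control, and 0.51 if charity rises by half the cash loss.

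**The case against.** The strongest reply is that an omnibus test followed by contrasts, with multiplicity adjustment over several subscales, is conventional for a secondary outcome. The gate costs little power by itself. The largest losses rest on a Holm family the article does not define, on the first and strictest Holm step, and on a charity effect of zero, whereas the Incentives section expects charity to help. Low follow-up limits power with or without the gate: the direct test reaches only 0.59 at 0.4 SD. The article does not say that group means or intervals will be withheld, and Multimedia Appendix 2, which is not shown, may add detail.

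Most of this stands as a limit on size. It does not answer the estimation point: the contrasts are expressly conditional, and imprecision is a reason to show the interval.

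A reader might go further in three ways that the documents do not support.

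- *That a loss of motivation could not affect whether incentives are kept.* The abstract's "If components prove to be efficacious, they will be included in a revised version of the app" and the similar sentence under Strengths and Limitations are statements of intent. Neither is a formal decision rule, and neither says motivation will be disregarded. The latter section also plans a randomized trial of the revised app.
- *That benefit faces a lower bar than harm.* This would set a primary outcome against a secondary one. Within motivation the gate is symmetric: a gain under charity meets the same test as a loss under cash.
- *That intrinsic motivation should be exempt from Holm.* This is a trade-off between power and false alarms, and the calculations do not settle it.

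**Conclusion.** The concern holds as a point about estimation. The section names incentive versus control as its leading comparison and then makes it conditional on another test. Under an even spread of 181 responders, the interval half-width is about 0.36 SD, so a non-significant omnibus result cannot exclude a moderate loss of intrinsic motivation under cash, and the stated plan would leave that loss unestimated.

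The power cost of the gate alone is modest: 0.51 against 0.59 at 0.4 SD, with charity equal to control. The figure of 0.33 applies only if Holm over about five subscales bears on the omnibus P values and no other subscale has cleared an earlier step. It reflects the adjustment and should not be charged to the gate. Effect sizes, number of subscales and arm sizes at follow-up are assumptions. The concern applies to cash, since the article does not raise it for charity.

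**What to change.** In the Secondary Analyses section:

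1. Report cash versus control and charity versus control on intrinsic motivation, each with a 95% confidence interval, whatever the omnibus result.
2. Keep the Holm-adjusted tests as the basis for any claim of significance, and say which P values form the Holm family.
3. State that a non-significant test is not evidence that motivation was unaffected, and that the interval shows which losses remain compatible with the data.

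No new data are needed. The article says that analyses start after its publication and that allocation stays encrypted until the analysis script is final, so the change can still be made blind. Because the analyses were prespecified and data collection has finished, it should be recorded as a dated change, as was done for the move to GEE. The downside is that two unadjusted intervals appear beside adjusted tests. They must be labelled as estimates, not confirmatory tests.
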